## Abstract

**Introduction:**

Biofeedback is a non-pharmacological treatment option valued for its minimal risk of adverse events and offers a safe alternative for individuals seeking preventive care for migraine. Despite level A evidence for migraine prevention, biofeedback treatment is still unavailable to most patients. We developed a novel medical device (Cerebri) for multimodal biofeedback treatment that omits the need for healthcare personnel involvement. Cerebri consists of a smartphone application (app) and two wireless sensors. Unique in its approach, the Cerebri app seamlessly integrates three biofeedback modalities – heart rate variability, temperature, and electromyography – making it a comprehensive, therapist-independent solution for non-pharmacological migraine management.

**Methods:**

Biofeedback therapy using Cerebri for the prevention of migraine attacks in adults with episodic migraine (The BioCer study) is an open-label, randomized, waitlist-controlled, multicenter trial. This study investigates the safety and efficacy of daily home-based biofeedback sessions using the Cerebri device. A total of 286 participants will be randomized to either a 12-week intervention arm or waitlist control arm. The primary outcome is the change in the mean number of migraine days from baseline to the last 28-day period during the treatment phase in the treatment group compared with the control group. The primary outcome variable is prospectively collected through daily eDiary entries. A limitation is the inability to conduct a sham-controlled trial of biofeedback.

**Ethics and Dissemination:**

Approval from the ethics committee and competent authorities was obtained prior to study initiation. Participation is voluntary and informed and written consent is obtained prior to inclusion. The results of this trial will be published in peer-reviewed international medical journals and communicated to patients and healthcare personnel through the relevant channels.

**Trial registration numbers:**

EUDAMED: CIV-NO-22-08-040446

REK (Regional Committees for Medical and Health Research Ethics): 502734 Date of approval 2022-10-14

Trial registration: NCT05616741, 2022-11-15,
https://clinicaltrials.gov/study/NCT05616741

## Introduction

Migraine is the second most disabling disorder worldwide and incurs enormous societal costs, estimated to exceed €50 billion per year in the EU alone.
^
1
^
^,^
^
2
^ Frequent migraine attacks warrant preventive treatment. A multitude of preventive pharmacological options are available; however, there are several barriers to effective treatment. For instance, one study reported that over two-thirds of patients discontinued their prophylactic migraine medication after six months, and more than 80% after a year, due to either a lack of efficacy or adverse reactions.
^
3
^

Several non-pharmacological behavioral interventions for migraine, such as biofeedback, have been highlighted as non-invasive prophylactic treatment regimens with a low risk of negative side effects, which can be an alternative or adjunct to pharmacological therapies. Biofeedback combined with relaxation training is listed with Grade A level evidence for migraine prevention in the 2000 guidelines from the American Academy of Neurology.
^
4
^ This has been continued in the updated 2021 American Headache Society consensus statement, which also suggests mobile health (mHealth) application-based approaches for delivering biobehavioural treatments to increase patient access and participation.
^
5
^

Biofeedback utilizes technologies and equipment to monitor physiological processes that are usually considered involuntary and modulated without conscious awareness. Presented with real-time feedback on these processes, users can learn to exercise control over them, which in turn has a beneficial effect on the migraine symptom burden. Despite its effectiveness, biofeedback has limited accessibility. The high financial costs of having a therapist instructing the procedure, necessary equipment, and patient travelling costs are likely to contribute to this. To our knowledge, no therapist-independent migraine biofeedback treatment with proven efficacy is currently available.
^
6
^

To address this gap, a multimodal biofeedback system, the Cerebri system, has been developed for therapist-independent home-based use. Unique to this product, the Cerebri application (app) seamlessly integrates three biofeedback modalities: heart rate variability (HRV), temperature, and electromyography (EMG), making it a comprehensive, home-based solution for non-pharmacological migraine management. The device is a product of a thorough development process, including a hardware feasibility study
^
7
^ and three development studies on progenitor versions of the system with short test periods.
^
8
^
^–^
^
10
^ In addition, prior to the initiation of this trial, a feasibility study with 3-month follow-up was performed.
^
11
^

## Protocol

### Study objectives and endpoints

The objective of this study is to investigate the efficacy and safety of a 12-week daily use of the Cerebri biofeedback device as compared to a waitlist control in adults with episodic migraine.

Primary efficacy endpoint

The primary endpoint is the change in the mean number of migraine days from baseline to the last 28-day period (week 9–12) during the treatment phase in the treatment group compared to the wait-list control group.

Secondary efficacy endpoints

The key secondary endpoint analyses are changes in mean number of migraine days in week 1–4 and week 5–8, change in mean migraine intensity, proportion of 30% responders, change in acute migraine drug treatment use, and change in subject-reported headache-related disability. Exploratory and descriptive endpoints include changes in weekly migraine days, mean headache days per 28-day period, eDiary and biofeedback session adherence, and mean Patient Global Impression of Change (PGI-C) scores. Additionally, changes in the mean number of migraine days during the extended biofeedback period will be assessed.

Safety endpoints

Description of the frequency and severity of treatment-emergent adverse events (AEs), adverse device effects (ADEs), serious adverse device effects (SADEs), and unexpected serious adverse side effects (USADEs) is included. In the case of pregnant participants, at inclusion or acknowledged during participation, no additional monitoring of maternal or fetal health is instituted. In such cases, participants are asked if they agree to be followed up until the end of pregnancy to collect data on any pregnancy complications and fetal outcome data.

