**Figure 1. f1:**
[figure not shown]
Flow chart of the BioCer study.

Eligible participants are randomly allocated to the treatment or waitlist groups. The treatment group receives the medical device by postal service, and a treatment period of 12 weeks is initiated on the first day of completing a biofeedback session. Participants in the waitlist group complete daily eDiary entries for 12 weeks from the day of randomization.

Both arms are invited to participate for a 12-week extension period. Participants randomly allocated to the waiting list are offered the possibility of entering a 12-week extension phase with biofeedback treatment. The 12-week extension period is initiated on the first day of the biofeedback training. The participants randomized to the intervention group are invited to a 12-week extension period after completing their 12-week biofeedback treatment, in which they continue with daily eDairy only.

Participants will not have access to the intervention at the end of the study. Beyond the voluntary 12-week extension period, there will be no long-term follow-up on safety and survival status, except in cases of pregnancy.

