**Figure 4. f4:**
[figure not shown]
A and B: Screen shots of the eDiary in the Cerebri mobile application.

A web-based dashboard solution enables study personnel to access a real-time overview of adherence to eDiary and biofeedback treatment. Thus, study personnel can identify and reach out to participants with low adherence. In the case of technical issues, a support service provided by the sponsor is available. The dashboard also includes information regarding the migraine/headache status on a given day and acute medication use. This information will be accessible to study personnel in the baseline period for rescreening purposes. Post randomization, only the adherence data is available.

Questionnaires

Subjects are asked to complete validated questionnaires at the end of each 28-day period to measure the headache-related impact on the quality of life and their impression of treatment efficacy. The questionnaires used in this trial are the Migraine-Specific Quality-of-Life Questionnaire (MSQ) v2.1
^
13
^ and the Patient Global Impression of Change (PGI-C).
^
14
^ The MSQ is copyrighted and registered with the United States Library of Congress by Glaxo Wellcome, Inc. A written permission for use is obtained prior to use.

Electronic patient record

Patient records are the source of information regarding medical history, current medications in use, and previous trials of prophylactic migraine treatment acquired during visit 1. Alterations in health status, including treatment-emergent adverse events during trial participation are registered in the medical records.

Study-specific electronic case report form (eCRF)

An eCRF applying the WebCRF3 software (version 3) (
https://webcrf3.medisin.ntnu.no) was developed for this study. The webCRF software is provided and maintained by the Unit for Applied Clinical Research (AKF) at the Faculty of Medicine and Health Sciences, NTNU. Data collected during study visits, telephone consultations, and safety information are entered. Data are stored in a pseudo-anonymous manner, and each study participant is identified using a unique study identification (ID) number. An open-source alternative OpenClinica (
https://www.openclinica.com/get-free-community-edition-software) is able to perform an equivalent function as WebCRF3.

Study monitoring

No data-monitoring committee is appointed for this study. An independent Data Monitor will be used for review of the study in accordance with a Monitoring Plan.

Data management

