For the efficacy analysis, the full analysis set includes all randomized participants and constitutes the intention-to-treat (ITT) population. The per protocol (PP) population includes all randomized participants without protocol deviations.

Analysis dataset 1 is defined as the data from the 16-week period for all randomized participants and does not include extension period data. The 12-week post-randomization period in the biofeedback arm starts on the date of the first biofeedback session. Data lock for the evaluation of efficacy endpoints can be performed upon the completion of this dataset.

The safety data set includes all participants exposed to the biofeedback device.

Primary endpoint analysis

Analysis of the study endpoints will be performed in the ITT (all randomized subjects) and PP populations.

The primary endpoint variable is migraine days. The operational definition used for the analysis will be prespecified in the SAP.

The planned analysis strategy involves a mixed logistic regression model which will include all available daily eDiary entries. The mixed logistic regression model will be used to estimate the difference in the change from baseline in the mean number of migraine days per 28-day period between the treatment and waitlist groups. The model will include the presence or absence of migraine on each day from the baseline and 12-weeks post randomization periods as a dependent binary variable, treatment allocation, time period (baseline, week 1-4, week 5-8 and week 9-12) and an interaction term between treatment allocation and post-randomisation time-periods are included as categorical fixed effects, together with the stratification variable (concomitant preventive medication use). The patient ID will be included as a random effect. The site of inclusion will also be assessed as a potential random effect prior to the unblinding of the statistician to the treatment allocation. The model does not require explicit imputation, as mixed models yield unbiased estimates under the assumption that data are missing at random. This assumption will be assessed and sensitivity analyses considered if warranted.

The primary effect estimate will be the model-based estimates of the difference in change from baseline in mean monthly migraine days between the treatment and waitlist groups, presented with a 95% confidence interval.

Baseline variables that are considered to be highly predictive of outcomes will be discussed and identified

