*a priori* and described in the SAP. These variables will be included in multivariate analysis. The SAP will also detail the analysis strategies for the secondary outcomes. Post hoc stratified analyses by sex (women vs. men) and assessment of sex interaction will be conducted.

The statistical analysis plan includes predefined sensitivity analyses, restricting the primary analysis to the per-protocol set and, if feasible, subgroup analyses according to adherence status. Specifically:
•Participants in the interventional group with >90% biofeedback adherence in all three 28-day periods will be compared with the remaining participants in the interventional arm with lower adherence.•Participants in the interventional group with >90% adherence during weeks 1–4 will be compared with the remaining participants in the interventional arm with lower adherence in that same period.

Safety data

Safety objectives will be assessed by collecting data on treatment-emergent adverse events encountered during biofeedback training, including adverse events (AEs), serious adverse events (SAEs), adverse device effects (ADEs), serious adverse device effects (SADEs), and unanticipated SADEs (USADEs), and by evaluating the frequency and severity of these occurrences.

All data on treatment-emergent adverse events, ADEs, SADEs, and USADEs will be categorized and summarized. The frequency and severity of treatment-emergent AEs, ADEs, SADEs, and USADEs will be summarized for all enrolled participants and the entire duration of the intervention. Adverse events occurring more than once in individual participants will also be summarized and presented descriptively.

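### The objective sets safety against the waitlist, but the stated safety set, event window and endpoint plan no such comparison, and the safety population is defined in two conflicting ways

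*Protocol article*

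**What the plan says.** Under Study objectives and endpoints, the objective is to investigate the "efficacy and safety of a 12-week daily use of the Cerebri biofeedback device as compared to a waitlist control". As worded, the waitlist is the comparator for both efficacy and safety. The safety endpoint in the same section begins "Description of the frequency and severity of treatment-emergent adverse events (AEs), adverse device effects (ADEs" and goes on to the serious device effects. It names no contrast between arms.

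Under Statistical analysis, the paragraph on data analysis sets states: "The safety data set includes all participants exposed to the biofeedback device". The paragraph on safety data states: "Safety objectives will be assessed by collecting data on treatment-emergent adverse events encountered during biofeedback training". The next paragraph says that the frequency and severity of events "will be summarized for all enrolled participants and the entire duration of the intervention".

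Under Study design: "Participants in the waitlist group complete daily eDiary entries for 12 weeks from the day of randomization". They may then enter an optional 12-week extension with biofeedback.

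Under Data collection, the text on the electronic patient record says: "Alterations in health status, including treatment-emergent adverse events during trial participation are registered in the medical records". That sentence is not limited to one arm. The eCRF takes data from visits and telephone consultations as well as safety information. Telephone calls are planned at weeks 2, 4 and 8, with adherence as their stated purpose.

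**The concern.** The objective names a comparator, and the analysis rules then remove it. During the randomized period the waitlist arm has no device and no training, so its participants belong neither to the safety set nor to the window in which events are assessed. They can enter the set only later, through the voluntary extension, and then as treated people rather than controls.

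At stake is the interpretation of non-specific events. Over 12 weeks some participants will have infections, musculoskeletal complaints or serious events that have nothing to do with the device. Without a concurrent rate, these are listed as treatment-emergent with nothing to set them against, and a modest excess caused by the device would look the same as background. The trial already has a randomized untreated arm that could supply that rate.

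There is also a plain inconsistency about whom the safety summary covers. Device-exposed participants and all enrolled participants are different populations.

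**Working it through.** **1. The plan's own figure.** The only sample size is for efficacy: d = 0.4, two-sided alpha 0.05, power 0.80, 30% dropout, total 286 (Statistical analysis, Sample size). With a two-sample t-test and 1:1 allocation (the ratio is not stated, so this is an assumption), n = 99.08, rounded up to 100 per arm, 200 in total. Then 200 / (1 − 0.30) = 285.7, or 286, which is 143 per arm. The figure reproduces and is not at issue. The document gives no figure for safety.

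**2. The safety statements side by side, for the 12 randomized weeks.**

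| Place | What it covers | Does a waitlist participant count? |
|---|---|---|
| Objective | Safety against the waitlist | Yes, as control |
| Safety endpoint | Description of events | No contrast named |
| Safety data set | Device-exposed participants | No |
| Event collection | Events during biofeedback training | No, there is no training |
| Event summary | All enrolled, over the duration of the intervention | By population yes, by window no |
| Electronic patient record | Health changes during participation | Possibly recorded, no analysis named |

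The number of concurrent unexposed controls in the safety set is 0, so that set yields no risk difference or ratio against the waitlist.

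**3. What the exposed-only set can support.** It gives a one-group description. For example, with no events of a given kind among n exposed, the one-sided 95% upper bound on the risk is 1 − 0.05^(1/n). For n = 143 this is 2.1%. For n = 286, if every waitlist participant also used the device, it is 1.0%.

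**4. What a by-arm table would give.** The documents state no adverse event rate, so background risks of 10%, 20% and 30% are assumed, equal in both arms. The 95% CI half-width for the risk difference is 1.96 × √(2p(1 − p)/n).

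| Background risk p | n = 143 per arm | n = 100 per arm (after 30% dropout) |
|---|---|---|
| 10% | 1.96 × √(0.18/143) = 7.0 points | 1.96 × √(0.18/100) = 8.3 points |
| 20% | 1.96 × √(0.32/143) = 9.3 points | 1.96 × √(0.32/100) = 11.1 points |
| 30% | 1.96 × √(0.42/143) = 10.6 points | 1.96 × √(0.42/100) = 12.7 points |

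Such a comparison would be coarse, but it would show a large excess of common events. The plan as written produces no estimate at all.

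**The case against.** The strongest reply is that the safety endpoint is descriptive, the hypotheses concern migraine days only, and the comparative reading rests on one sentence that joins efficacy and safety. The abstract mentions safety without a comparator. On that view the sentence is loosely worded, and rewording it is all that the text strictly requires. This stands in part, and it is why the fix offers rewording as an alternative. It does not remove the conflict, because the objective, the safety set and the event summary cannot all hold as they are.

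A second reply is that summarising all enrolled participants brings the waitlist back. It does not: the same sentence ties the summary to the intervention period and to treatment-emergent events, and a waitlist participant has neither before crossover.

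A third reply is that table layouts belong in the full plan and SAP, which are not shown. That is right for layouts. The point here is that stated rules on set and window remove the comparator that the objective names.

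A reader might also infer more than the text supports:

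- *Waitlist events go unrecorded, or the trial is unable to compare safety.* The text on patient records covers trial participation without limiting it to one arm, so the data may exist.
- *Headache worsening cannot be separated from background.* Both arms keep the eDiary, and migraine days, intensity and acute drug use are compared by arm.
- *The Discussion's remarks on mislearning show a risk of the device.* They concern false sham feedback, which no arm receives.
- *Extension exposure will be pooled with the randomized arm.* The article does not say so. It only sets no separation for safety.

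Effects that need a sensor, such as contact reactions to its material, have essentially no waitlist background, so a control adds little for them.

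**Conclusion.** The point holds as an inconsistency with a practical consequence. The objective promises safety against the waitlist. The safety set, the event window and the endpoint plan no such comparison, and the two descriptions of the safety population disagree. The loss concerns non-specific adverse events and serious events, for which the plan as written has no concurrent comparator. It does not extend to headache outcomes, and the documents do not show that the comparison is impossible, only that none is planned.

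The size is illustrative: a risk difference known to within about 7 to 11 points (143 per arm) or 8 to 13 points (100 per arm), against no estimate. This rests on assumed 1:1 allocation and assumed background risks of 10% to 30%. The sample size and the primary analysis are unaffected. The matter should be corrected, but it does not threaten the main efficacy conclusion.

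**What to change.** Reconcile the objective, the safety data set and the two paragraphs on safety data, in one of two ways.

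**Preferred: keep the comparison.**
- Define a safety set of all randomized participants for the 12 randomized weeks. State when that window starts in each arm, because the treatment arm's 12 weeks run from the first biofeedback session and the waitlist's from randomization.
- Elicit AEs and SAEs with the same questions in both arms at the existing contacts (weeks 2, 4 and 8) and once more at the end of week 12, since the week 8 call misses weeks 9 to 12.
- Tabulate AEs and SAEs by randomized arm, with risk differences and 95% CIs, as description rather than as a test.
- Report ADEs, SADEs and USADEs in exposed participants, and show the waitlist arm's extension exposure separately.

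**Alternative: drop the comparison.** Remove safety from the objective's comparison with the waitlist, state that it is descriptive in device-exposed participants, and correct the reference to all enrolled participants to match.

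The first option costs a scripted question at contacts already planned, one added query at the end of week 12, slightly more event recording in about 143 waitlist participants, and one more table. The second costs only wording, but gives up the background rate.

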## Methods and analysis

### Study design

This is an open-label, randomized, waitlist-controlled, multicenter trial. The study design follows the standard for clinical investigation of medical devices for human subjects – good clinical practice (ISO 14155:2020) – and the relevant trial guidelines of the International Headache Society.
^
12
^ Reporting follows the CONSORT guidelines.

The total duration of study participation is 16 weeks, with the possibility of a 12-week extension period (
Figure 1). After the screening visit, if eligible, the participants are assigned to a baseline period of a minimum of four weeks in accordance with the guidelines.
^
12
^ During the baseline period, participants maintain a daily headache diary in the Cerebri smartphone app. Upon completion of the baseline period, the participants were rescreened for eligibility prior to randomization. This design, where the baseline period also serves as a screening period, enables rescreening based on eDiary entries. This is the recommended approach for enrolling RCTs on episodic migraine.
^
12
^ Participants deemed ineligible at the point of rescreening, or who withdraw from or are lost to follow-up during the baseline period, are categorized as screening failures and are excluded from further participation.

